## Abstract

**Background:**

Large-scale implementation of evidence-based psychotherapies (EBPs) such as cognitive processing therapy (CPT) for posttraumatic stress disorder can have a tremendous impact on mental and physical health, healthcare utilization, and quality of life. While many mental health systems (MHS) have invested heavily in programs to implement EBPs, few eligible patients receive EBPs in routine care settings, and clinicians do not appear to deliver the full treatment protocol to many of their patients. Emerging evidence suggests that when CPT and other EBPs are delivered at low levels of fidelity, clinical outcomes are negatively impacted. Thus, identifying strategies to improve and sustain the delivery of CPT and other EBPs is critical. Existing literature has suggested two competing strategies to promote sustainability. One emphasizes fidelity to the treatment protocol through ongoing consultation and fidelity monitoring. The other focuses on improving the fit and effectiveness of these treatments through appropriate adaptations to the treatment or the clinical setting through a process of data-driven, continuous quality improvement. Neither has been evaluated in terms of impact on sustained implementation.

**Methods:**

To compare these approaches on the key sustainability outcomes and provide initial guidance on sustainability strategies, we propose a cluster randomized trial with mental health clinics (*n* = 32) in three diverse MHSs that have implemented CPT. Cohorts of clinicians and clinical managers will participate in 1 year of a fidelity oriented learning collaborative or 1 year of a continuous quality improvement-oriented learning collaborative. Patient-level PTSD symptom change, CPT fidelity and adaptation, penetration, and clinics’ capacity to deliver EBP will be examined. Survey and interview data will also be collected to investigate multilevel influences on the success of the two learning collaborative strategies. This research will be conducted by a team of investigators with expertise in CPT implementation, mixed method research strategies, quality improvement, and implementation science, with input from stakeholders in each participating MHS.

**Discussion:**

It will have broad implications for supporting ongoing delivery of EBPs in mental health and healthcare systems and settings. The resulting products have the potential to significantly improve efforts to ensure ongoing high quality implementation and consumer access to EBPs.

**Trial registration:**

NCT02449421. Registered 02/09/2015

## Background

Thousands of public sector clinicians have been trained to deliver evidence-based psychotherapies (EBPs) due to recent mandates and investments in implementation [1, 2]. Patients treated during EBP training programs experience substantial symptom improvement [3–5]. Despite this progress, efforts to implement and sustain EBPs in these systems face significant challenges. One finding is that penetration (integration of a practice within a service setting and its subsystems) is low [6, 7]. Veteran Affairs clinicians rarely cite established contraindications as reasons not to offer EBPs; [8, 9] instead, they cite challenging symptom profiles, a need for more consultation, and clinic-level barriers [10, 11]. A second challenge is that research suggests that fidelity (adherence to prescribed elements of treatment and competence/skill of delivery) [12] may be low when these interventions are implemented [13, 14]. Challenges in implementing EBPs lead to adaptation without systematic efforts to understand the impact on symptoms and other outcomes [15, 16]. While some adaptation and latitude in EBP delivery may be appropriate [17], effective [18–21], or promote implementation [22], other adaptations result in discontinuation of core elements [15], integration of non-evidence-based strategies [13, 23], and worse outcomes [24, 25]. In addition to these challenges, local capacity can impact sustainability and quality of delivery. A significant minority of clinician trainees do not meet established EBP competency criteria but deliver EBP protocols or EBP elements in their practice [11, 13, 15]. Turnover and organizational context can also impact sustained EBP delivery [26, 27]. Patient access and clinical outcomes may suffer as a result [23, 24, 28–30]. Thus, in the context of routine care, improvement, rather than maintenance, [31] of clinical outcomes may be an appropriate goal. Finally, while EBPs are cost-effective [32], the budget impact of supporting implementation can be a barrier [33–35].

Failure to provide EBPs to those with PTSD can have a significant public health impact. Consequences of inadequate treatment include risk of suicide, overuse of healthcare, work absenteeism, reduced productivity, unemployment, and family disruption [36, 37]. Cognitive processing therapy (CPT), which has been implemented in at least eight countries and in mental health systems throughout the world, has a strong evidence base and is effective with a variety of patient populations [19, 20, 38–42]. The current study will aid in identifying strategies to promote sustainability of CPT and improve patient-level outcomes, thereby informing efforts to implement EBPs for psychiatric disorders more broadly.

Researchers have identified serious gaps in knowledge regarding best practices for improving and sustaining EBPs in routine care [43–45]. There have been few, if any, experimental investigations of strategies to sustain EBPs. Few studies on sustainability have assessed a full range of the key outcomes, such as patient-level mental health outcomes [46]. To address these gaps and identify effective strategies for sustaining EBPs in routine care, we seek to compare two promising yet different implementation strategies (ISs), fidelity-oriented consultation, and continuous quality improvement.

### Proposed interventions

Existing research and theory suggest two contrasting ISs, one oriented to fidelity and the other to mutual adaptation and quality improvement. These strategies have potentially different mechanisms, costs, and relative benefits that could impact their fit in differing contexts.

### Fidelity-oriented learning collaborative (FID)

Studies show that without consistent follow-up or ongoing support of clinicians to promote fidelity after initial training, the training effects quickly dissipate [47, 48]. Although a recent meta-analysis demonstrated no overall link between observer-rated fidelity and symptom change across a range of treatments and disorders, when analyses were conducted to avoid the potential temporal confound between fidelity and symptom change and establish the temporal precedence of fidelity, two aspects of fidelity, adherence to the protocol and competence (skill of delivery) in early CBT sessions were associated with subsequent decreases in depression [49]. Later research suggested that fidelity to the key aspects of CPT, as opposed to prescribed session elements, was associated with symptom change [50]. Other studies demonstrated patient-level benefits of fidelity-oriented support for EBPs as compared to general professional development-oriented support [51–53]. A FID strategy has been shown to lead to clinician achievement of benchmark levels of fidelity [54]. We would thus expect FID to impact clinical outcomes through CPT fidelity as a mechanism of change. Fidelity support also appears to impact other implementation outcomes, most notably sustained EBP capacity, delivery [55], and support activities [56]. Fidelity support has also been associated with lower staff turnover, which improves workforce capacity [53].

### Continuous quality improvement-oriented learning collaboratives (CQI)

Organization-level barriers to implementation are commonly found in routine care settings and may impact sustainability [4, 26, 57, 58]. In our study on CPT training consultation in Canada, [59] in Texas, and in the US VA [10, 11], clinicians cited organization-level challenges to delivering EBPs for PTSD and hesitance about offering EBPs, due in part to a perceived lack of fit between the treatment and the patients [9]. These problems may contribute to the low rates of penetration [6, 7]. The Dynamic Sustainability Framework (DSF) suggests that the dynamic “fit” between an intervention and its delivery context is critical to sustainability [60]. It rejects the assumption that deviation from the protocol leads to decreased benefit and advocates for mutual adaptation and continuous refinement of EBPs in real world contexts [60]. CQI, identified in the DSF as a facilitator of sustainability, has been used successfully in healthcare and mental health settings [61, 62] and has guided EBP adaptation [63]. CQI also fosters learning organizations, which are more likely to improve care and innovate [64]. We therefore expect that the mechanisms by which CQI impacts clinical outcomes are EBP adaptation and functioning as a learning organization.

While high-level leadership support is strong, and structural and policy level changes and investments have been made to support implementation within many systems, [2] the individual clinicians who must ultimately deliver treatments have identified idiosyncratic challenges at local levels. The locally oriented, clinician-led approach of CQI-oriented learning collaboratives [61] (LCs) may facilitate sustainability, but this possibility remains unexamined [65]. On the other hand, greater time, cost, and personnel burden [66, 67] may be a barrier to CQI, and whether the CQI process and resulting adaptations lead to more effective treatment and implementation is unknown. To answer these questions, we will conduct a mixed method, type-III hybrid design, which allows simultaneous study of ISs, their mechanisms, and clinical outcomes [68].

### Summary of the proposed project

Clinics in three mental health systems that have implemented CPT for PTSD will submit baseline session recordings and patient data for at least two patients (*n* = 192) before random assignment to either 12 months of FID (*n* = 16 clinics, 48 clinicians, 192 patients), or CQI (*n* = 16 clinics, 48 clinicians, 192 patients). Outcomes will include patient self-reported PTSD symptom outcomes (primary); independent fidelity ratings; and penetration, adaptation, and capacity to deliver CPT [46, 69]. We will also investigate engagement in, credibility and costs of, and satisfaction with each IS [mechanisms by which the interventions impact patient outcomes] as well as contextual factors that may impact sustainability. The mixed method design will include qualitative methods for a richer understanding of the process and outcomes for each of the ISs [70]. This study will capitalize on infrastructure created for a previous trial comparing EBP consultation strategies [59] as well as existing infrastructure in the participating mental health systems and strong collaborative relationships and experience with each participating mental health system. The study has the potential to advance implementation science beyond observational studies of EBP sustainability by providing much-needed information on the effectiveness of interventions to promote long-term EBP implementation.

## Methods

### Summary

We plan to randomize clinics and associated clinicians in three mental health systems that have implemented CPT for at least 2 years into one of two conditions: CQI-LC or FID. Implementation outcomes will be assessed. ISs will be compared over the course of the 1-year intervention phase and a 1-year follow-up. Mechanisms of action and budget impact will also be explored. A phased rollout of the ISs will allow baseline data to serve as within and across subject comparison data. Potential individual and contextual influences on sustainability will also be assessed through surveys and interviews to elucidate how these factors may impact CPT delivery and IS engagement and outcomes.

### Recruitment

Participating clinics and clinicians will be drawn from the three mental health systems: the VA Canada Operational Stress Injury (OSI) National Network and affiliated clinics (VAC), the United States VA system, and the State of Texas (TX). Each of these systems has implemented CPT in the past several years, with standardized training across the networks which includes an initial workshop followed by 6 months of consultation. As Table 1 indicates, the systems are diverse in terms of clinician backgrounds, patient populations, and financing.

**Table 1 Tab1:** Characteristics of participating mental health systems

Source	No. of clinicians available for recruitment	No. of clinics (planned/ available)	Clinic type/population	Clinician degrees	Payment/reimbursement	Penetration
VA Canada OSI Network (VAC)	134 OSI clinicians and contracted community clinicians, 65% received CPT provider status	11/38	VAC clinics and community-based/veterans and civilians	M.A., PhD/PsyD	Government veteran benefits, private insurance, self-pay for civilians	~60% of eligible patients (by self-report)
United States VA system (VA)	2996 trained, 73% reached provider status	11/138	VA hospitals and clinics/veterans	PhD/PsyD, MSW, MD	Typically VA benefits, TriCare	112–20% eligible patients [6]
Texas (TX) Community MH Clinics	253 trained/53% reached CPT provider status	10/115	Civilians and rural veterans	MSW, LICSW, LPC, CART, MA, PhD/PsyD	Medicaid, VA Tricare, self-pay, private insurance	To be assessed

We plan to recruit and enroll an average of 3–4 clinicians per clinic across 32 clinics over the first 2 years of the study.

### Inclusion/exclusion criteria

We will recruit VAC and VA clinics, TX, and Canadian community clinics that participated in CPT training and have at least 4 clinicians eligible to participate. Clinics are defined as work units under the same supervisor or service line within an organization. Clinicians and supervisors who maintain a caseload will be eligible to participate in the study if they (1) are CPT-trained and provide psychotherapy to individuals with PTSD, (2) are willing to record therapy sessions, provide work samples for baseline assessment, and complete baseline surveys, and (3) have internet access. We considered only enrolling clinicians who had achieved a certain level of CPT adherence (e.g., “provider status”) but recognized that stakeholders need to understand how to improve EBP delivery among *all* clinicians who deliver EBPs within the system, including the 23–47% of clinicians (Table 1) who receive training but do not achieve provider status. Their inclusion allows assessment of ISs’ ability to improve capacity to deliver high quality CPT.

Eligible patient participants are Veterans or non-Veterans (1) diagnosed by their clinicians to have current PTSD, with a minimum PTSD checklist (PCL) score of 33 (based on the most current validation and cutoff scores that indicate a likely PTSD diagnosis for the PCL-5) [71] 2) who have not previously received CPT, and (3) are willing to consent to completing symptom measures and have their sessions audio recorded and reviewed. Patients are permitted to continue other psychotherapies if the treatment is not specifically focused on PTSD. Ineligible patients are those ineligible for CPT based on the state of research evidence as follows: (1) current uncontrolled psychotic or bipolar disorder, (2) [past month] substance dependence requiring daily use or detoxification (eligibility can be revisited if individuals enter recovery), (3) imminent suicide/homicide risk requiring immediate intervention, and (4) cognitive impairment precluding therapy engagement (e.g., significantly impaired memory or attention).

### Randomization and timeline

Randomization will occur at the clinic level. Given the relatively small number of clinics, a stratified randomization procedure will be used to match the ISs (after baseline) on size (# of clinicians in each clinic) and system. The statistician will create a block for each combination of covariates and assign each clinic to the appropriate block. Simple randomization will occur for clinics within each block. As illustrated in the timeline, ISs will occur in three waves, and within each wave, clinics will be randomized further into immediate or delayed (6 months) start. This will facilitate a comparison with no IS [72] using symptom and session data collected from the baseline phase of the delayed start group. Administrative data from before and during the IS phase will facilitate further comparison of symptom change for patients seen before vs. during ISs. During baseline and to keep the delayed start group engaged, we will offer webinars to introduce study technology and provide general updates on CPT research findings (with no guidance for actual practice). Incentives for engagement in baseline include written fidelity feedback from one baseline session after the IS phase starts, clinician and clinic-level gifts for providing baseline data, and CE credits for webinars.

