##### Sample size justification and power calculations

We require a sufficient sample to detect non-inferiority based on a clinically significant change of 5 points on the PCL [101, 102]. Calculations of a design effect (measure of how the design effects the standard error of the parameters) [103, 104] accounted for clustering. We computed intraclass correlations (ICC) with repeated observations of CPT patients at the clinic (*ρ* = 0.12), clinician (*ρ* = 0.16), and patient (*ρ* = 0.38) level in our prior research in Canada and VA, yielding a design effect of up to 2.32 [83]. Power to detect a clinically meaningful difference on PTSD symptom scores over time, taking the design effect into account, is .80 in a two-sided test, using repeated measures, with an alpha-level of 0.05 and a standard deviation (sd) of 7 points (based on prior research), for a sample size during the IS phase of 288 patients (144 per condition) within 32 clusters. In the proposed study, we expect to randomize 32 clinics, with an average of three clinicians per clinic and at least four patients per clinician during both the IS and follow-up phase. For each patient, PTSD symptoms will be measured at nine time points, as it is typical to assess symptoms frequently in CPT (baseline, every other session, post-treatment, and follow-up). To very conservatively account for potential patient-level attrition and missing data during treatment, we estimated an average of four observations per patient. Furthermore, we considered the longer study length, rates of turnover in each system, attrition rate in previous studies, balanced with participation in an active intervention, system support, and incentives, to anticipate substantial, but not unmanageable, attrition. Full participation in the IS and follow-up would yield 384 patients and at least 1536 observations, and thus, we could see a clinician attrition rate of 33% while remaining adequately powered to detect non-inferiority of CQI, and superiority of the ISs as compared to the baseline/non-IS phase data (an additional 2 patients per clinician; up to 192 patients). This projection exceeds the rate of attrition seen in our prior studies in these systems and is sufficient to test for non-inferiority on OQ measure as a secondary analysis, as the OQ-45 has an RCI of 14 (sd = 16) [105]. Finally, the sample will allow for a stable estimate of a fidelity based on the recommended *G* = .70–.80 level of dependability) [106].

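### Simple randomization inside the size-by-system blocks gives no balance beyond chance, so the stated matching and the planned 16:16 split do not follow from it

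*Protocol article*

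**What the plan says.** The section Randomization and timeline sets the unit: "Randomization will occur at the clinic level". It gives the small number of clinics as the reason for stratifying, and the aim as follows: "a stratified randomization procedure will be used to match the ISs (after baseline) on size (# of clinicians in each clinic) and system". The mechanics are then given in two steps. First: "The statistician will create a block for each combination of covariates and assign each clinic to the appropriate block". Second: "Simple randomization will occur for clinics within each block". No fixed split, permuted block, minimization or other restriction is stated anywhere in the article. A second randomization follows: "within each wave, clinics will be randomized further into immediate or delayed (6 months) start".

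The Summary of the proposed project plans "16 clinics, 48 clinicians, 192 patients" for each strategy, an exact 1:1 division. The sample size section repeats the total ("we expect to randomize 32 clinics, with an average of three clinicians per clinic and at least four patients per clinician") and bases power on 144 patients in each condition. Table 1 plans 11 clinics in VAC, 11 in the US VA and 10 in Texas.

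Under Analytic strategy (Aim 1), system enters the model as a clinic-level variable. Clinic size is not among the covariates named there, although that list is given as examples.

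**The concern.** The purpose and the method do not fit together. Stratification balances arms only if allocation inside each stratum is restricted, for example by fixing how many clinics go to each arm. Simple randomization is the unrestricted case. Sorting clinics into blocks and then assigning each one independently gives the same allocation distribution as not sorting them at all.

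This is not a detail left to a fuller document. The article names the within-block method, and the method it names cannot deliver the matching it announces. A statistician following the sentence would toss coins, and allocation cannot be redone once clinics are randomized.

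The systems differ on quantities that the trial tests. In Table 1, provider status ranges from 53% to 73% of trained clinicians, which bears on hypothesis 6. Penetration, the subject of hypothesis 5, is put at about 60% in VAC, against an upper figure of 20% in the US VA. A lopsided system mix would be unwelcome with only 32 units.

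**Working it through.** **Inputs.** 32 clinics, with 11, 11 and 10 by system (Table 1); three clinicians per clinic and four patients per clinician (sample size section). Fair 1:1 assignment is assumed.

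**The plan's own figure.** 32 / 2 = 16 clinics per arm; 16 × 3 = 48 clinicians; 48 × 4 = 192 patients. The stated arm sizes reproduce and require an exact 16:16 split.

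**Distribution under the stated method.** The number of clinics in FID is a sum of Binomial(n_s, 0.5) over strata s. This is Binomial(32, 0.5) whatever the strata.

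- P(16:16) = C(32,16) / 2^32 = 0.140
- P(18:14 or worse) = 2 × P(X ≥ 18) = 0.597
- P(20:12 or worse) = 2 × P(X ≥ 20) = 0.215
- P(22:10 or worse) = 2 × P(X ≥ 22) = 0.050

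At 20:12 the arms would hold 60 and 36 clinicians, and 240 and 144 patients.

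**By system.**

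- 11 clinics, 8 or more in one arm: 2 × (165 + 55 + 11 + 1) / 2048 = 0.227
- 10 clinics, 8 or more in one arm: 2 × (45 + 10 + 1) / 1024 = 0.109
- At least one of the three systems: 1 − (1 − 0.227)² × (1 − 0.109) = 0.47
- All three split as evenly as possible: 0.451 × 0.451 × 0.246 = 0.050

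**By system and size.** The size categories are not stated. If there were two, with strata of 6, 5, 6, 5, 5 and 5 (an assumption), the chance that at least one stratum falls wholly in one arm is 1 − (31/32)² × (15/16)⁴ = 0.28.

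**Effect on power.** With clinics of equal size, a k:(32 − k) split has efficiency 4k(32 − k) / 32² relative to 16:16. For a test with nominal power 0.80 at two-sided 0.05, power becomes Φ((1.960 + 0.842) × √efficiency − 1.960).

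| Split | Efficiency | Power |
|---|---|---|
| 16:16 | 1.000 | 80.0% |
| 18:14 | 0.984 | 79.4% |
| 20:12 | 0.938 | 77.4% |
| 22:10 | 0.859 | 73.8% |

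This takes the stated 0.80 at face value. The protocol's own inputs (5 points, SD 7, design effect 2.32, 144 per arm) give 0.978 in a simple two-sample calculation, and 0.971 at 20:12. That discrepancy is a separate question; on those inputs the loss is smaller still.

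**What restriction within strata would achieve.** Suppose an even split is forced in each stratum, with the odd clinic assigned at random.

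- Three system strata (11, 11, 10): 16:16 with probability 0.50, never worse than 17:15.
- Six assumed strata (6, 5, 6, 5, 5, 5): 16:16 with probability C(4,2) / 2⁴ = 0.375, never worse than 18:14.
- Permuted blocks of 4 in the 10-clinic system: the last block is half filled, both of its clinics fall in the same arm with probability 2/6 = 1/3, and the split is then 6:4.

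**The case against.** The strongest reply is that the authors meant a random equal split within each block and used the term loosely. The aim of matching, the timing after baseline and the planned 16:16 all fit that reading. It may be right, but the article does not say so, and the sentence still needs correction.

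The second reply concerns harm, and most of it stands. A reader might infer that the comparison is biased or confounded by system. The documents do not support that: allocation is random, so any imbalance arises by chance, and the primary model adjusts for system. A reader might also infer a serious loss of power, but the table above shows a modest one.

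Two points survive this reply. Clinic size, the other matching factor, is not a named covariate. Its effect may be limited, since enrolment averages 3–4 clinicians per clinic. Also, the additional analyses (section 3.I.5) test system by strategy by time. If a system splits 8:3 or 8:2, only two or three clinics remain on one side of that contrast, and adjustment does not restore the lost information.

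A reader might further infer that restricting allocation within strata would guarantee 16:16, or 5:5 in the 10-clinic system. It would not: odd strata and incomplete blocks leave some imbalance. Nor is there a sparsity argument in multiplying system, wave, arm and start time into 36 cells, because arm and start time are results of allocation and not strata.

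**Conclusion.** The sentence is wrong as written: the method it names gives no balance beyond chance on the two factors that stratification is meant to match. The planned 16:16 would be missed in 86% of allocations, and all three systems would be split as evenly as possible in only about 5%. The consequences are chance imbalance on system and clinic size, a modest power loss and weaker system-by-strategy comparisons. The validity of the randomized comparison is not affected.

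These figures assume fair, independent assignment and the planned clinic counts in Table 1. The power figures also assume clinics of equal size. If an equal split within blocks was intended, the fault lies in the wording alone, but it is wording that determines how clinics are allocated.

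**What to change.** Replace the sentence with a restricted scheme. The preferable choice is covariate-constrained randomization over system and clinic size: draw at random from the allocations that meet a preset balance rule, with an overall 16:16 constraint as far as allocation in waves allows. The alternative is a forced even split, or concealed permuted blocks, within a small number of strata, pairing the odd strata so that their spare clinics go to opposite arms. Restriction within strata alone limits imbalance without guaranteeing exact equality, so the text should not promise it.

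State the size categories and how the immediate or delayed start randomization nests within the scheme. Name clinic size as a covariate alongside system, so that the analysis reflects the factors used in allocation.

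The cost is a different allocation routine run by the same statistician and a few sentences of text. The downside is slightly more set-up work and the need to keep the sequence concealed, because restricted schemes are more predictable than coin tosses.
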